## Study design

The study design uses a feasibility study model with a mixed-method research approach. The study will occur in two phases. Phase 1 will consist of focus groups with the primary aims to identify and assess current facilitators and barriers to cooking behavior in the community to inform the study. Phase 2 will consist of the cooking intervention and clinical assessment visits at baseline and at two follow up periods, 6 weeks and 12 weeks post intervention. Overall, phase 2 will have four different time points: baseline clinical visit (TP_0_), cooking intervention (TP_1_), second clinical visit occurring 6 weeks after the intervention concludes (TP_2_), and a subsequent clinical visit occurring 12 weeks post intervention (TP_3_). The protocol for D.C. COOKS follows the SPIRIT checklist [27]. Table 2 shows the overall study plan and design.

**Table 2 Tab2:** Study plan and timeline

	Phase 1		Phase 2											
Schedule of events and study plan	Enrollment for phase 1	Focus groups (community site)	Enrollment for phase 2	Clinical visit #1 TP_0_	Community cooking class—2-h session weekly for 6 weeks (community site) TP_1_						Home cooking experience	Clinical visit #2 TP_2_	Home cooking experience	Clinical visit #3 TP_3_
Week				− 4 to 0	1	2	3	4	5	6	7-11	12	13-17	18
Eligibility screen	X		X											
Informed consent		X		X										
Focus group discussion		X												
History and physical, vital signs, anthropometrics Blood draw for CVD biomarkers				X								X		X
Interview with study team				X			X			X		X		X
Dietician assessment				X								X		X
AMPS cooking skill assessment				X								X		
Daily cooking journal					X	X	X	X	X	X	X	X	X	X
Participant surveys		X		X								X		X
Community cooking intervention					X	X	X	X	X	X				

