### Study procedures

In phase 1 of this study, participants (*n* = 20) will take part in one of two moderated focus groups designed to explore participants’ experiences with food and dietary selections and cooking behavior. Within this phase, participants will also take self-administered surveys related to cooking behavior, non-dietary health behaviors, and psychosocial factors. Open-ended (qualitative) questions for the focus groups were selected to elicit feedback regarding facilitators and barriers to cooking and perceptions about the feasibility of the intervention regarding (1) obtaining food for cooking, (2) use of cooking skills, (3) social norms around home cooking, (4) personal attitudes and knowledge, (5) preferences for recipes/food choice, and (6) preferences for intervention timing. Focus group feedback will also be used to modify the survey, if needed. Data analysis is anticipated to occur over a 1-month time period and the results of data analysis will inform the second phase. Specifically, the data captured from this phase will inform phase 2 in terms of recipe selection for intervention, local locations to source food for the intervention, anticipated concerns about intervention location, and schedule of sessions.

Phase 2 of the study consists of two parts: clinical visits, surveys, and interviews at pre (TP_0_) and post intervention intervals (TP_2_, TP_3_) and the cooking intervention (TP_1_). We will recruit thirty (*n* = 30) participants for this phase. Phase 2 will start with a baseline visit (TP_0_) prior to the intervention start. During this visit, a clinical history and physical examination, objective cooking assessment, dietician interview, and phlebotomy for CVD biomarkers will take place. Following completion of baseline visits for all participants, the community intervention will start with all participants who have completed the initial clinical visit. We estimate that it will take 4 weeks for all participants to complete their baseline visit. Participants will return for the second clinical visit at 6 weeks and 12 weeks post the intervention. To ensure that time of participation and days of follow up in the study are equal among participants, those who enroll and come in for their baseline visit at the earliest time point (week 4) will return for follow up visits prior to participants who completed baseline visits closer to the end of the initial time point (T_0_).

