## Study outcome measures

### Primary outcomes

The primary outcomes for this study are feasibility measures, home cooking behavior, and objective evaluation of cooking motor and process skills. In order to determine feasibility of the cooking intervention, we are collecting information on number of screened participants, number of participants enrolled, attendance at intervention sessions, and attrition rates. Attendance will be taken at each session. At a minimum, participants are counted as an attendee when one full intervention session has been completed. Completers of the intervention will be defined as participants who complete all six intervention sessions. Dropouts for the study will be defined as those who attend the first clinical visit, but do not attend any intervention session by the date of the final session. Attrition rates will be determined from the number of participants who stopped participating divided by the average number of participants at each time point, and over the total study period (see Fig. 4 for time points). We anticipate that our attrition rates will be at or below 33%, which is the reported attrition rate for this target population based on members of the research team’s experience recruiting from wards 7 and 8 [34]. Feasibility success will be achieved if the majority of participants (> 50%) reach 50% participation (3/6 sessions). This is based on two reports in the literature of cooking intervention studies among African-Americans in which this attendance metric was met [13, 15]. Information collected on feasibility and cooking behavior and skills will allow for appropriate sample size calculations for future studies.

Cooking behavior will be determined through multiple variables to provide a convergence of data. Using paper cooking diaries, participants will be instructed to start daily recording of home cooking following the initial clinical visit and will stop after the last visit, for a total collection time of 18 weeks. The design for the cooking diaries is fixed-schedule (once per day). Each daily entry will consist of marking the frequency of cooking at home, as well as commenting on enjoyment, interest [47], and perception of cooking skills.

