For the survey responses related to the primary outcomes, facilitators, and barriers to cooking (DC CHOC, CAFPS, CES), question items deemed as positively related to facilitating cooking will have a sum of scores calculated and then divided by total number of respondents. Survey items deemed as negatively related to cooking (barriers) will be reverse scored to determine mean scores. Within DC CHOC Survey, responses for cooking perception will be dichotomized as agreement with cooking if response is ≥ 5, as reported in Wolfson 2016 [71].

From the cooking diaries, daily cooking frequency amounts will be aggregated into cooking frequency for each week of the study, the average at each time point of phase 2 for each participant. Cooking frequency at each time point will also be dichotomized based on the average cooking frequency per week of 10.8 out of 21 possible meals, as reported in a national survey of U.S. adults [71].

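### The cooking diary, one of several measures of the primary cooking-behavior outcome, has conflicting start rules and no assured pre-intervention value, although the analysis calls for one at TP0

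*Protocol article*

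**What the plan says.** All references are to the protocol article.

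- **Primary outcomes:** "participants will be instructed to start daily recording of home cooking following the initial clinical visit and will stop after the last visit". The duration stated alongside this rule is "for a total collection time of 18 weeks". The section also says that several variables together describe cooking behavior.
- **Study design, Table 2:** clinical visit #1 (TP0) falls in weeks −4 to 0. The row "Daily cooking journal" is blank in that column and marked for weeks 1 to 6, 7–11, 12, 13–17 and 18. Clinical visit #3 (TP3) is in week 18.
- **Study procedures:** "We estimate that it will take 4 weeks for all participants to complete their baseline visit". Classes have a common start: "Following completion of baseline visits for all participants, the community intervention will start". Follow-up visits are to be staggered by baseline date: "To ensure that time of participation and days of follow up in the study are equal among participants".
- **Data analysis:** phase 2 has four time points. Daily diary counts become weekly frequencies and "the average at each time point of phase 2 for each participant". Frequency at each time point is then dichotomised at 10.8 of 21 weekly meals.

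**The concern.** The diary's start, its length and its planned analysis do not fit together. The sentence that sets the start at the baseline visit carries a duration that fits only a start in the week of the first class. A site following Table 2 would begin recording when classes begin. A site following the text would begin up to about four weeks sooner, with the lead time set by the date of each participant's visit. Neither version assures that everyone has diary days before the first class, yet the analysis needs a TP0 diary value for each participant.

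The study sets out to look at home cooking before and after the classes, and Table 5 lists the diary among the primary outcome measures. If recording starts with the classes, the diary can describe cooking during and after the intervention but not its change from before. Diary days not recorded before session 1 cannot be recovered.

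**Working it through.** **Inputs.** Baseline visit in week b, with b from −4 to 0; last visit in week 18; diary weeks as marked (all from Table 2). Stated total 18 weeks (Primary outcomes). Classes in weeks 1 to 6 (Table 2). Counts are in whole weeks.

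**Step 1: reproduce the stated figure.** Add the weeks marked in the Table 2 diary row: 6 (weeks 1–6) + 5 (weeks 7–11) + 1 (week 12) + 5 (weeks 13–17) + 1 (week 18) = 18. The stated total is reproduced exactly, with no week before the first class.

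**Step 2: apply the rule in the text.** Total = 18 − b; weeks before class = −b.

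**Step 3: test whether staggering rescues the 18 weeks.** If every participant has exactly 18 weeks from baseline, TP3 falls in week 18 + b, which is 18 + b − 6 = 12 + b weeks after the intervention ends.

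| Baseline week b | Pre-class diary weeks (−b) | Total if TP3 is at week 18 (18 − b) | TP3 week if total is held at 18 (18 + b) | Weeks post intervention (12 + b) |
|---|---|---|---|---|
| −4 | 4 | 22 | 14 | 8 |
| −3 | 3 | 21 | 15 | 9 |
| −2 | 2 | 20 | 16 | 10 |
| −1 | 1 | 19 | 17 | 11 |
| 0 | 0 | 18 | 18 | 12 |

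The text and the 18 weeks agree only for someone seen at week 0, who has no pre-class diary week. Holding 18 weeks for everyone puts TP3 at 8 to 12 weeks post intervention, whereas Study design describes "a subsequent clinical visit occurring 12 weeks post intervention (TP_3"). Staggering only within the single week that Table 2 gives to TP3 would absorb at most about 1 of the 4 weeks of spread.

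**Step 4: set the schedule against the analysis.** On the natural reading, Table 2's diary weeks split into weeks 1–6 (TP1), 7–12 (TP2) and 13–18 (TP3), and 6 + 6 + 6 = 18. All 18 weeks are then used and none is left for TP0, the fourth time point.

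**Step 5: how many would have a short run-in under the text.** The spread of visit dates is not given, so this is an assumption. With visits even over 28 days, 7/28 = 25% have fewer than 7 pre-class days, or 7.5 of 30. If 10% of visits fell in the final week it would be 3 of 30; if 50%, 15 of 30.

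**The case against.** A reader might infer that the study's main cooking measure is lost at baseline, that change in cooking therefore cannot be shown, and that any comparison would mix a recall item with a diary. The article does not support this. It never calls the diary the main measure; it relies on several convergent variables, and Table 5 lists the diary beside other instruments. Home cooking frequency over the prior 7 days is asked with the same survey questions at TP0, TP2 and TP3, so a like-for-like pre/post comparison exists. Nowhere does the article plan to compare recall at TP0 with a later diary value. These points stand, and they confine the loss to one instrument.

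The setting also limits the consequence. This is a single-arm feasibility study whose stated success criterion is attendance (more than half of participants reaching 3 of 6 sessions). Inferential statistics are exploratory, with no conclusion on effectiveness. No sample size or confirmatory test depends on a diary baseline. This stands too, and argues against ranking the problem as critical.

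It can further be said that the blank cell proves little: its column is headed by the visit, and Table 2 has no column for the interval between visit and week 1. That is fair as to the cell alone. But the 18-week total matches weeks 1 to 18 independently of that cell, and the text rule does not yield 18 weeks for anyone seen before week 0.

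Finally, the article intends equal time in study. Step 3 shows that this intention cannot hold together with a 12-week post-intervention visit for everyone, so it adds to what must be reconciled.

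**Conclusion.** The contradiction is established from the article's own figures. The text implies 18 to 22 weeks of recording; the stated 18 weeks and Table 2 fit only weeks 1 to 18. Pre-class diary time is none as scheduled in Table 2, and 0 to about 4 weeks under the text, while the analysis asks for a diary average and a dichotomised value at TP0. The 18-to-22 range assumes that TP3 stays at week 18. The share of participants with a short run-in depends on visit dates that are not given.

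The loss is the diary's own pre/post change, its variability for planning later studies, and the intended convergence of measures at baseline. Change in cooking frequency by 7-day recall is unaffected. Severity is moderate: worth settling before the first class, but no threat to the feasibility criterion.

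**What to change.** Reconcile Study design (Table 2), Study procedures, Primary outcomes and Data analysis:

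1. State one diary start, at TP0, and mark the period from that visit to week 1 in Table 2.
2. Schedule baseline visits so that each participant has a short diary run-in before session 1, for example 7 days. The exact length is a choice for the sponsor.
3. Define the TP0 diary value from those days as a rate per recorded day, so that unequal run-ins are comparable, and scale it to a week for the 10.8-meal cut.
4. Restate the duration. If TP3 stays at week 18 and baseline visits end by week −1, it is 18 + 1 = 19 to 18 + 4 = 22 weeks.
5. Reconcile the equal-participation sentence with the stated timing of the follow-up visits.

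The cost is modest but more than wording: baseline visits close about a week earlier, and each participant keeps the diary for one to four weeks beyond the 18 now stated. Trial status says that recruitment was still to begin, so on the article's timeline the change could precede the first class.

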**Fig. 3 Fig3:**
[figure not shown]
Cooking diary components by topics. Participants will be instructed to respond for each day of the week

As stated earlier, a current gap in the literature is whether participation and engagement level in cooking behavior is expected to vary by participant’s baseline cooking skill. To our knowledge, assessment of baseline cooking skill has not been described in published cooking intervention studies as a participant characteristic. Assessment of Motor and Process Skills (AMPS) is a kitchen performance assessment test delivered by occupational therapists to assess an individual’s performance skills (motor and process). For each task, motor and process skills are evaluated. Motor skills involve hand movement and coordination. Process skills involve the actions used to organize and adapt behavior over time in order to complete a task. The AMPS test will be administered by trained occupational therapists in the Department of Rehabilitation kitchen at the NIH Clinical Center at baseline and the 6-week clinical visit. Analysis of AMPS will be done with a computerized scoring system where the correction for the score is based on skilled item difficulty, task challenge, and rater severity [51]. Because the test encourages participants to choose familiar tasks, it is participant centered. Additionally, AMPS has been validated for use in an African-American adult population [52].

### Secondary outcomes

Health behaviors are often socially patterned [67]. Moreover, dietary behaviors are likely influenced by tradition and a shared history that is passed from generations which then determine intrapersonal (taste preferences), interpersonal (cultural and familial paradigms), and community set norms [67]. Therefore, secondary outcomes measured are related to psychosocial factors, the neighborhood food environment, dietary intake, and health behaviors, such as physical activity and sleep quality. Figure 2 illustrates our conceptual model of potential relationships between primary and secondary outcomes. Table 5 provides a list of primary and secondary study measures with instrument type and description of measurement.

**Table 5 Tab5:** Table of study measures with instrument type and description of measurement

Measurement	Type of instrument(s)	Description
Primary outcomes		
Facilitators and barriers to cooking		
Cooking diaries	Daily self-administered data collection	Daily responses to cooking frequency questions will be used
Cooking self-efficacy scale (CSES) [14, 53]	Self-administered 7 item instrument	CSES assesses the degree of confidence in performing basic cooking activities on a 5-point Likert scale
Psychosocial factors related to cooking [50]	Self-administered 32 questions (61 items) D.C. CHOC Cooking Survey	D. C. CHOC is a self-administered 32 question (61 items) survey to assess psychosocial determinants and developmental exposure to cooking as well as confidence for certain cooking techniques and food shopping. It will also capture cooking frequency over the last 7 days.
Food agency [17]	Self-administered 28 item Cooking and Food Provisioning Action Scale (CAFPAS)	CAFPAS is a 28 item instrument with 3 sub-scales ( food self-efficacy—13 items, food attitude—10 items, perceived influence of non-food barriers on provisioning—5 items). The scale has undergone face and construct validity and reliability testing, with Cronbach’s alpha = 0.7
Cooking skills [51]	Assessment of Motor and Process Skills (AMPS)	AMPS is a kitchen performance assessment test delivered by occupational therapists to assess an individual’s performance skills. The AMPS will be conducted at baseline and 6-week clinic visit.
Feasibility measures		
Attrition	Number of participants that complete the study	Attrition will be based on the number of participants at the start and remaining at the end of the study, as well as at each time point. Attrition rates will be determined from the number of participants who stopped participating divided by the average number of participants at each time point, and over the total study period
Attendance	Attendance record at each intervention session using study log	Attendance will be taken at each intervention session and rates will be analyzed to determine the desired dosage (how much, how often and at what interval) for each participant by their characteristics
Participant burden	Observations of research team and participant feedback	Participant burden will be determined by data collection assessments, research team’s perception of participants’ understanding of questions and data collection methods, and if participants respond with missing or unusable data. The study team will also assess if participants have enough time and capacity to complete data collection procedures.
Treatment fidelity [54]	Guidelines for treatment fidelity from the NIH Behavior Change Consortium workgroup on treatment of fidelity	Treatment fidelity assessment grid will be used to determine implementation of the intervention. Cooking diaries and interviews will also be used as a measure of implementation/intervention fidelity.
Secondary outcomes		
Social network index [55, 56]	Self-administered 12 item measure	SNI is a self-administered 12-item instrument that assesses participation in 12 types of social relationships. There are three measures within the SNI: number of high-contact roles (network diversity), number of people in social network, and number of embedded networks.
Health promoting Lifestyle Profile II (HPLP-II) [57]	Self-administered 52-item instrument	The HPLP-II is a self-administered 52-item instrument that measures the frequency of self-reported healthy behaviors. It consists of 6 subscales: physical activity, spiritual growth, health responsibility, interpersonal relations, nutrition, and stress management (including sleep quality).
Perceived stress [58]	Perceived stress scale (PSS) is a self-administered 10 item instrument	PSS measures an individual’s perceptions about the nature of events and their relationship to coping resources of that individual. This 10 item tool uses a 5 point Likert scale for each item.
Neighborhood factors		
MESA Neighborhood Perception of Healthy Food Availability Scale [59]	Self-administered shortened 3 item scale (the original being 6-item).	This scale is used to calculate perceived healthy food availability in the neighborhood, which is defined as within a 20-min walk or one mile distance from the individual’s home.
Perception of Neighborhood Food Retail Outlets [60]	Self-administered 9 item questionnaire	This tool consists of 9 items and tests types of retail outlets available within the neighborhood, which is defined as within a 20-min walk or one mile distance from the individual’s home.
Neighborhood satisfaction [61]	Single question with 5 answer choices	Neighborhood satisfaction will be measured with the question, “All things considered, would you say you are very satisfied, satisfied, dissatisfied, very dissatisfied, or neutral - neither satisfied nor dissatisfied with your neighborhood as a place to live?”
Food purchasing practices [61]	Grocery receipts	Grocery receipts will be collected at intervention sessions and follow up CC visits, to assess overall dietary quality and utilization of food store type
	Food purchasing practices	Food purchasing questionnaire measures frequency of major food shopping with 11 different types of store options. It also inquires about mode of transportation for that major food shopping trip.
	Food Away from Home frequency	Food away from home will be assessed by one question from CD-NHANES-DBQ, 2015 (During the past 7 days, how many meals did you get that were prepared away from home in places such as restaurants, fast food places, food stands, grocery stores, or from vending machines?), whereas the meal could mean breakfast, lunch or dinner.
Self-rated health [62]	Self-administered 1 item measure	Self-rated health is assessed through one question and it measures the general health state or change in state which could be associated with outcomes of interest
Sleep quality assessment [63]	Pittsburgh Sleep Quality Index (PSQI)	PSQI is a 9-item self-administered measure that assesses the quality and patterns of sleep. PSQI has seven subscales and altogether they create a total score of sleep quality.
Physical activity [64]	International Physical Activity Questionnaire (IPAQ)-Short form	IPAQ short form is a self-administered 7 item measure that assesses the types and intensity of physical activity and also the time spent while sitting.
HEI & Mediterranean diet adherence screener [65, 66]	24-h food frequency questionnaire	A nutritional assessment will be done by a member of the dietician team from the CC Nutrition Department using 24 hour dietary recall. This will provide information regarding dietary patterns and eating behaviors. Study staff (registered dieticians) will analyze the food records using Nutrition Data System for Research (NDS-R) software for energy, protein, carbohydrate, fat, alcohol, caffeine, and micronutrient intake. A composite diet quality score (a measure of nutritional status and adherence to dietary guidelines) will be calculated using the Healthy Eating Index.
	14-item Mediterranean diet adherence screener (MEDAS)	MEDAS is a 14 item questionnaire that assesses adherence to the Mediterranean diet. Photographs of portions and serving sizes are used to facilitate accurate completion. Validation of the MEDAS questionnaire and test-retest reliability for English version has been conducted.
Family meals ()	Family Meal frequency	Family meal socialization will be assessed by one question from CDC-NHANES-DBQ 2015 (During the past 7 days, how many meals did all or most of your family sit down and eat together at home?), where the meal could mean breakfast, lunch or dinner
CVD biomarkers	- BMI - Blood pressure - A1C - Lipid screen - CBC with differential - Glucose (fasting) - Insulin (fasting) - Advanced lipid panel (fasting) - CRP, IL-6	CVD biomarker collection duet to known role of dietary behaviors on CVD risk factors
Anthropometrics	Waist circumference and waist to hip measurement	Waist circumference (at the top of the iliac crest) and hip circumference (at the maximum protuberance of the buttocks) will be measured in triplicate with the average of measurements used as data for clinical visit time point

All secondary outcomes will be obtained through self-administered questionnaires, except for dietary intake. Dietary intake will be measured using a 24-h recall of food and drink intake collected by the nutrition team from the NIH Clinical Center Nutrition Department. During the interview, the nutrition staff member will ascertain the content and quantity of dietary intake, as well as inclusion of home cooked versus purchased foods. This will be done to determine baseline and post intervention diet quality of home cooked food, not just general diet quality. Data from the 24-h recall will also provide information regarding dietary patterns. Study staff (registered dieticians) will analyze the food records using Nutrition Data System for Research (NDS-R) software for energy, protein, carbohydrate, fat, alcohol, caffeine, and micronutrient intake [68]. A composite diet quality score ranging from 0 to 100 will be calculated using the Healthy Eating Index, HEI-2015 (https://epi.grants.cancer.gov/hei/) [65]. Calculated HEI score assesses the extent to which a participant follows the 2015–2020 Dietary Guidelines for Americans (DGA). Because the HEI-2015 aggregates dietary components, it provides a hypothesis-oriented approach to determine participants’ dietary pattern. The Mediterranean Diet score will be determined by the Mediterranean Diet Adherence Screener (MEDAS) [66].

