The current gaps in the literature around the role of behavior may also occur because assessing behavioral mechanisms for cooking intervention outcomes can be complex. For instance, the concept of cooking skills is representative of a confluence of skills: perceptual and conceptual, mechanical, academic (knowledge of preparing raw and cooked foods), and cognitive planning skills. Additionally, for each individual, the interplay between these skills may differ based on their intrapersonal or interpersonal experiences. Lastly, the absence of a detectable effect may not result from the cooking intervention being ineffective, but rather could be a consequence of the logistical difficulties in standardizing and evaluating complex health interventions, especially in an experimental process [24]. Ideal participation and engagement level in an intervention to achieve an increase in cooking frequency is not well defined in the literature. Furthermore, it is unclear if participation and engagement level is expected to vary between individuals, or by objectively determined baseline cooking skill.

Feasibility allows for focus on real-world acceptability and implementation, while involving key stakeholders (study participants) at each stage of the exploration process [25]. A feasibility study approach also allows for process evaluations that provide a detailed understanding of complex interventions by examining their implementation, mechanism of impact, and context [26]. In relation to facilitators and barriers to cooking, understanding aspects of feasibility could help inform behavioral mechanisms that can explain cooking intervention results. The purpose of this protocol paper is to present the design and conceptualization of a cooking intervention feasibility study among African-American adults living within a food desert to evaluate home cooking behaviors pre and post a community cooking intervention.

Based on the limited body of evidence regarding the implementation and biobehavioral outcomes of cooking interventions, the aims for the D.C. COOKS with Heart study are to:
Determine feasibility of delivery of cooking behavior intervention for African-American adults at risk for CVD as described by Bowen et al. (25):

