### Cooking intervention

The 6-week cooking intervention (TP_1_) in phase 2 will be delivered by a chef who is professionally trained, licensed, and certified regarding local food safety regulations. The intervention site will be a community-based kitchen site located within ward 7 or 8. Participants will be divided into two groups of 15. Each group will meet weekly at the kitchen site for a 90-min culinary education session. There will be no group assignment; participants may choose which group to attend, but can only attend one group session per week. The minimum number of participants required for delivery of the intervention will be one participant per session. In case of the need for an emergency medication administration for unknown food allergies, all sessions will be staffed with clinical research team members. Medical students trained in culinary medicine will also be present during each session to assist participants as needed. Table 3 provides an overview of the DC COOKS with Heart cooking intervention sessions.

**Table 3 Tab3:** D.C. COOKS with Heart cooking intervention

Goal	Deliver cooking behavior intervention in a community setting
Type	In-person, chef-led instruction
Duration	6-week intervention with weekly 2-h sessions
Structure of sessions	Introduction and discussion of recipes and ingredients Cooking of recipes in groups Shared meal experience
Assessments	Semi-structured interviews (phone administered) Treatment fidelity Behavior change taxonomy (BCT)

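### Attendance at one fixed weekly schedule cannot determine a desired frequency, interval or individual dosage, as Table 5 says it will

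*Protocol article*

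**What the plan says.** Table 5 of the protocol article (printed in the Secondary outcomes section) lists attendance among the feasibility measures, in the primary-outcome part of the table. After saying that attendance is logged at each session, the row states that "rates will be analyzed to determine the desired dosage (how much, how often and at what interval) for each participant by their characteristics". That names three aspects of dose and promises an answer at the level of the individual.

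The schedule is given in the section Cooking intervention: "Each group will meet weekly at the kitchen site for a 90-min culinary education session". Table 3 in the same section describes a "6-week intervention with weekly 2-h sessions", and Table 2 (Study design) shows one session in each of weeks 1 to 6. On allocation, the text says: "There will be no group assignment; participants may choose which group to attend, but can only attend one group session per week". There is one curriculum, no comparison group, and no assignment to a different number or spacing of sessions.

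Under Gaps in the literature, the article gives a reason for interest in dose: "Ideal participation and engagement level in an intervention to achieve an increase in cooking frequency is not well defined in the literature".

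**The concern.** To learn how much, how often or how far apart sessions should be, those quantities must differ between participants in a way that can be separated from the participants' own circumstances. Here the plan fixes all three for everyone. What remains is how many sessions each person came to, which reflects motivation, availability and barriers, and possibly how much the person already cooks.

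At stake is what may be concluded from the attendance log. If a figure for the desired number or spacing of sessions were reported by subgroup, it would describe who was able and willing to come to a weekly class. It would carry no information about any other schedule. The abstract says that the study should supply information for planning later interventions, so the limits of this measure should be stated where it is defined.

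**Working it through.** The plan gives no figure for desired dosage, so there is none to reproduce. The check is whether each part of the stated use can be obtained from the design.

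**Inputs.** Six sessions, one per week, at most one attended per week, no assignment (Cooking intervention; Tables 2 and 3). Attendance is recorded at each session (Primary outcomes; Table 5).

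**Step 1: what is offered.** Number = 6, frequency = 1 per week, interval = 1 week, for every participant and in both groups. Each takes one value, so there is no variation by design.

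**Step 2: what is attended.** Let k be the number attended (0 to 6).

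- Attended frequency over the six weeks = k/6 per week. It is a rescaling of k, so how often cannot be separated from how much.
- For k ≥ 2, mean gap = (last week attended − first week attended)/(k − 1) = 1 + m/(k − 1), where m is the number of sessions missed between the first and last attended, and m ≤ 6 − k.

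Listing all 2^6 = 64 attend/miss patterns gives:

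| k | patterns | possible mean gap (weeks) |
|---|---|---|
| 0 | 1 | not defined |
| 1 | 6 | not defined |
| 2 | 15 | 1, 2, 3, 4, 5 |
| 3 | 20 | 1, 1.5, 2, 2.5 |
| 4 | 15 | 1, 1.33, 1.67 |
| 5 | 6 | 1, 1.25 |
| 6 | 1 | 1 |

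Spacing thus does vary among attenders. Counted in whole weeks, every departure from one week comes from m, that is, from absence. For example, with k = 3 the widest mean gap is 1 + 3/2 = 2.5 weeks, and it requires all three missed sessions to fall between the first and last attended. A participant with k = 6 always has weekly spacing. Moving between the two groups could shift a gap by days, but that too is the participant's choice.

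**Step 3: spacing and content.** Table 4 gives each session its own topic. A missed week therefore removes material. It does not deliver the same content at a wider interval.

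**Step 4: for each participant.** Each person shows one pattern under one schedule. Nothing shows what the same person would have done, or gained, under another.

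**Side point.** Session length is 90 minutes in the Cooking intervention text and 2 hours in Tables 2 and 3. Six sessions come to 6 × 1.5 = 9 hours or 6 × 2 = 12 hours, so the amount delivered in hours is also not settled. These places must be reconciled.

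**The case against.** The strongest reply is that the row concerns sessions received, and these do vary in number and spacing, as the table in the working shows. That stands: it would be wrong to say that frequency and interval never vary in the data. They do not vary by design, and the variation that arises comes from absence or choice of group.

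A second reply is that desired need not mean effective. The row sits among feasibility measures and names no outcome. The stated aims include demand and adherence, and Phase 1 asks about preferred timing. On that reading the attendance log measures uptake, and self-selection is the thing of interest. This is a fair reading, although the remark on ideal participation under Gaps in the literature points the other way. It does not rescue the sentence, because attendance at one weekly schedule cannot show a preference for another frequency or interval.

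Third, the Data analysis section treats inferential statistics as exploratory and rules out conclusions on effectiveness, and the secondary aims in Table 1 are all exploratory. This limits the harm. It does not withdraw the aim of determining a dosage.

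A reader might infer that the investigators will set a future trial's schedule from these rates, or will present an attendance association as a dose effect. The documents do not support that. No section says so, and the onward use named under Primary outcomes is sample size calculation for later studies.

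**Conclusion.** The sentence is wrong as written, on either an effectiveness or a preference reading. The offered number, frequency and interval have one value each. Attended frequency is k/6, average spacing departs from weekly only through missed sessions or a change of group, and there is one pattern per person. A desired frequency, interval or individual dosage cannot be determined from this.

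The conclusion rests only on the schedule and allocation as the article states them; no assumed standard deviation or subgroup size enters. Severity is minor. The feasibility criterion (more than half of participants attending at least three of six sessions) and the sample of 30 do not depend on the sentence. The number and pattern of sessions attended, described by participant characteristics, remain legitimate and useful feasibility results.

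**What to change.** Reword the Attendance row of Table 5. Remove the clause about determining a desired dosage for each participant, and say instead:

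- The number of sessions attended (0 to 6) and the pattern of attendance, including gaps left by missed sessions, will be described overall and by baseline characteristics, with 95% intervals.
- Any relation between sessions attended and cooking frequency will be adjusted for baseline cooking frequency and reported as an exploratory association only, because adjustment does not remove confounding by motivation or availability.
- The frequency and interval of sessions are not tested by this design.

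No new data are needed: attendance is logged at every session, and cooking frequency over the prior 7 days is already collected at the baseline visit (Primary outcomes). The cost is one table cell and a smaller claim.
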